### Assessments

Follow-up visits will take place at weeks 4, 6, 12 and 24 (±1 week); the details of assessments are provided in table 4. At each visit, concomitant medications will be recorded, an AE check will be performed, compliance with antithyroid medication checked and FBC and thyroid function (TSH, FT4, FT3 and TRAb) will be assessed. Other assessments include goitre size assessment, eye examination, patient-reported quality of life measures (Graves’ Orbitopathy Quality of Life Instrument^4^ and Thyroid Patient-Reported Outcome^19^), specific antibody tests and other safety bloods (FBC, LFT). At the end of their participation in the trial, participants will be asked their opinion on which treatment allocation they received, and if they would recommend their treatment to a friend with the same condition. In addition, we plan to undertake exploratory analyses of lymphocyte subsets determined by flow cytometry and transcriptomic markers of plasma cells using quantitative reverse transcription-PCR.^20^

**Table 4 T4:** *S*chedule of assessments

Assessment/activity	Visit 1	Visits 2 & 3	Visit 4	Visit 5	Visit 6	Visit 7	Visit 8	Visit 9
			Day 0	Day 14 (±3 days)	4 weeks (±1 week)	6 weeks (±1 week)	12 weeks (±1 week)	24 weeks (±1 week)
Written informed consent	X							
Demographics & medical history	X							
Physical examination	X							
12-lead ECG	X							
Eye examination (CAS)	X							
Hepatitis B & C serology, HIV	X							
Bone chemistry	X							
Coombs, blood group, RBC phenotyping	X							
Pregnancy testing (females)	X						X	
COVID-19 vaccination offered		X X						
IMP infusion			X	X				
Weight	X	X	X	X	X	X	X	X
Resting pulse rate	X		X	X	X	X	X	X
Goitre size assessment	X		X			X	X	X
FBC	X		X	X	X	X	X	X
TSH, FT4, FT3, TRAb	X		X	X	X	X	X	X
U&E, LFT	X		X	X	X	X		
IgGAM	X		X			X	X	X
Height			X					
Eye examination (composite eye index)			X			X	X	X
Thyroid volume on USS			X					X
QoL questionnaires (GOQoL, ThyPRO)			X			X	X	X
TgAb, ATPO			X			X	X	X
Specific antibodies			X				X	X
Exploratory analysis sample			X			X	X	X
Vital signs			X	X				
Compliance with ATD			X	X	X	X	X	X
Concomitant medication		X	X	X	X	X	X	X
Adverse event reporting		X	X	X	X	X	X	X
Follow-up phone call			X	X				
End of trial questions								X

ATD, antithyroid drug; ATPO, antithyroid peroxidase; CAS, Clinical Activity Score; FBC, full blood count; GOQoL, Graves’ Orbitopathy Quality of Life Instrument; IMP, investigational medicinal product; LFT, liver function test; QoL, quality of life; RBC, red blood cell; TgAb, thyroglobulin antibodies; ThyPRO, Thyroid Patient-Reported Outcome; TRAb, TSH receptor antibodies; TSH, thyroid-stimulating hormone; U&E, urea and electrolytes; USS, ultrasound scan.

### Discontinuation of treatment and withdrawal

Participants who have completed one or more daratumumab/placebo infusions may remain on the trial but choose to discontinue treatment. These participants will continue to take part in the trial assessments as per the trial schedule of events. Alternatively, an investigator may discontinue a participant from receiving trial treatment at any time (until administration of second infusion is completed), if the investigator considers it necessary for any reason. Participants who withdraw from the trial after receiving IMP (full or part dose) will not be replaced. Participants who withdraw before IMP is given will be replaced.

### Safety reporting

AEs will be documented in patient medical notes before entry into the trial database. AEs judged by the investigator responsible for patient care as consistent with the usual clinical pattern for patients with severe Graves’ disease (eg, hyperthyroidism, hypothyroidism, tachycardia, bradycardia) will not be reported. Disease progression will be recorded as an AE only if it is more severe than expected in the trial population. AEs will be coded according to MedDRA classifications. All AEs meeting the criteria for seriousness will be reported by the investigator to the trial sponsor within 24 hours of awareness, and suspected unexpected serious adverse reactions will be reported to the Medicines and Healthcare products Regulatory Agency (MHRA) and Research Ethics Committee (REC) by the trial sponsor in line with regulatory reporting timelines.

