### Trial design

This is an adaptive, two-stage randomised phase IIa, single-centre clinical trial that will aim to recruit 30 patients with severe Graves’ disease from secondary care at the Newcastle upon Tyne Hospitals NHS Foundation Trust. It is a single-blinded trial in which participants will be blind to allocation. Recruitment start date: October 2021; planned end of trial (last patient last visit): April 2024.

Stage 1 is a dose–response study using four doses of daratumumab (9 mg/kg, 3 mg/kg, 1 mg/kg, 0.5 mg/kg) and a colourless, volume-matched placebo infusion in approximately 15 patients (ie, five groups of n=3, randomised in a 1:1:1:1:1 ratio using permuted random blocks without stratification) (figure 1).

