### Intervention

Each participant will receive two infusions, on day 0 and day 14 (±3 days). The prescribed daratumumab dose will be prepared in a 500 or 1000 mL bag of sodium chloride 0.9%, using the most recent available participant weight to calculate banded dose (see table 2 for volume and infusion rate). Each participant will be prescribed the same banded dose for both infusions, using the same weight for both. Where placebo is allocated, a volume-matched bag of sodium chloride 0.9% will be used. All participants will be pre-medicated with three non-IMPs, paracetamol (1 g orally), methylprednisolone (100 mg intravenously) and chlorphenamine (10 mg intravenously) at least 30 min prior to their allocated infusion.

**Table 2 T2:** Infusion rate table

Time (hour:min)	Rate (mL/hour)	Total volume at end of time (mL)
Stage 1 (1000 mL)		
1	80	80
2	160	240
3	240	480
4	320	800
4:40	320	1000
Stage 2 rate A (1000 mL)		
1	50	50
2	100	150
3	150	300
4	200	500
5	200	700
6	200	900
6:30	200	1000
Stage 2 rate B (500 mL)		
1	50	50
2	100	150
3	150	300
4	200	500

The maximum infusion rate of daratumumab was determined by the recommendation of the SmPC for daratumumab (DARZALEX 20 mg/mL concentrate for solution for infusion). For stage 1, all participants will receive the IMP/placebo diluted in 1000 mL sodium chloride 0.9% for both infusions. For stage 2, some patients may receive higher doses of daratumumab, so a more prolonged first infusion will be given to all participants. If participants have no IRRs during their first dose in stage 2, then the second dose may be given in 500 mL sodium chloride 0.9% with a faster infusion rate, in line with SmPC recommendations.

IMP, investigational medicinal product; IRRs, infusion-related reactions; SmPC, Summary of Product Characteristics.

Vital signs (pulse rate, blood pressure and temperature) will be recorded prior to the start of each infusion and every 15 min during the course of the infusion, and for 1 hour afterwards. Infusion-related reactions will be addressed as shown in table 3, and documented as an AE. Infusion charts will be completed to document compliance with prescribed dose. Participants will be followed up by phone approximately 2 days after each infusion visit to check for any AEs. After the day 14 visit, no further IMP will be administered. Patients will continue their regular medications, including antithyroid drugs and beta-blockers throughout the study, as deemed appropriate by the clinical team.

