**Table 3 T3:** Infusion-related reactions (IRRs)

Grade 4 reactions	Life-threatening	Stop and permanently discontinue infusion.
Grade 3 reactions	Severe, including: Tachycardia ≥120 BPM or drop in SBP ≥30 mm Hg over pre-infusion with symptoms Rise in SBP ≥30 mm Hg over pre-infusion or tachypnoea ≥24/min Hypoxia SaO_2_ <92%	Stop infusion until observations improve and restart at 50% of the infusion rate at which IRR occurred. If the patient does not experience additional symptoms, infusion rate escalation may be resumed at increments and intervals as appropriate. The procedure above should be repeated in the event of recurrence of grade 3 symptoms. After the infusion restart attempts, the IMP treatment will be permanently discontinued upon the third occurrence of a grade 3 or greater IRR.
Grade 1–2 reactions	Mild to moderate, including: nasal congestion cough chills throat irritation vomiting nausea	Stop infusion in case of clinically significant reaction only until observations improve and restart at 50% of the infusion rate at which IRR occurred. If the patient does not experience any further IRR symptoms, infusion rate escalation may be resumed at increments and intervals as clinically appropriate up to the maximum rate. Infusion does not need to be stopped if IRR is not clinically significant.

BPM, beats per minute; IMP, investigational medicinal product; SaO_2_, arterial oxygen saturation; SBP, systolic blood pressure.

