### Interim analyses and criteria for the premature termination of the trial

An interim analysis of dose–response will be conducted after 15 patients have provided 12-week follow-up data. To assess efficacy, a three-parameter Emax model will be fitted to the logarithm of the percentage change in TRAb from baseline to week 12 using the DoseFinding package in R^23 24^ in the dose–response population (participants analysed according to the amount of daratumumab received). This model is used to estimate the plateau effect and (1) the dose that gives a mean reduction of 50% and (2) the dose that gives 90% of the plateau effect. If the estimated plateau effect corresponds to >50% reduction in TRAb, the trial will continue with placebo and doses (1) and (2) defined above. If the estimated plateau corresponds to less than 25% reduction in TRAb, the trial will terminate early for lack of promising dose–response unless the Data Monitoring Committee (DMC) agrees that there has been an unequivocal improvement in serum thyroid hormone measurements in the active IMP versus placebo groups; if it is between 25% and 50% reduction, the trial will continue with doses of 9 mg/kg and a higher daratumumab dose (eg, 12 or 16 mg/kg as determined by safety data), plus placebo. Safety information will be taken into consideration in deciding stage 2 dose(s) and could over-ride the model-based dose recommendations.

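### An investigator not stated to be blinded decides which non-serious thyroid and heart-rate events go unreported, which could bias the safety comparison between arms

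*Protocol article*

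**What the plan says.** All references are to the protocol article.

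- **Safety reporting.** AEs that the treating investigator judges "consistent with the usual clinical pattern for patients with severe Graves’ disease (eg, hyperthyroidism, hypothyroidism, tachycardia, bradycardia) will not be reported". A related rule follows: "Disease progression will be recorded as an AE only if it is more severe than expected in the trial population". The same section says that AEs go into the medical notes before database entry, and that all serious AEs are reported to the sponsor within 24 hours.
- **Trial design.** "It is a single-blinded trial in which participants will be blind to allocation". The article does not state that investigators or AE assessors are blinded.
- **Table 1.** The safety objective is measured by adverse reactions to 24 weeks, together with immunoglobulins, specific antibodies and blood counts.
- **Interim analyses.** Safety information feeds into the choice of stage 2 doses and can displace the model-based recommendation. If the estimated plateau lies between 25% and 50%, safety data also determine which dose above 9 mg/kg is added.
- **Intervention and Table 3.** "Infusion-related reactions will be addressed as shown in table 3, and documented as an AE". Table 3 lists among the grade 3 criteria: "Tachycardia ≥120 BPM or drop in SBP ≥30 mm Hg over pre-infusion with symptoms".

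**The concern.** The named events are not plainly background noise in this trial. The Introduction explains that TRAb drives thyroid hormone overproduction and that daratumumab may lower TRAb quickly. Risk assessment and Intervention say that antithyroid drugs continue, as the clinical team sees fit. A fall in TRAb under continued antithyroid treatment makes hypothyroidism a foreseeable consequence of a drug that works. Tachycardia is both a feature of thyrotoxicosis and a sign listed for infusion reactions.

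The rule acts before reporting, so a non-serious event judged usual may never reach a causality assessment in the trial data. The judgement has no stated threshold, second reader or flag, and it may be made with knowledge of the allocation. What is at stake is the between-arm comparison of adverse reactions, which is a stated outcome and also informs dose decisions.

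**Working it through.** The article gives no figure on this point to reproduce. The check has three parts.

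**1. When does the filter distort the comparison?**

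Let *p* be the true event rate, taken as equal in both arms. Let *w*D and *w*P be the probabilities that an event is judged usual, and so dropped, on daratumumab and on placebo.

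- Reported rate in an arm = *p* × (1 − *w*)
- Reported difference, daratumumab minus placebo = *p* × (*w*P − *w*D)

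All values below are assumptions; none is in the article.

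| True rate *p* | *w*D = 50%, *w*P = 50% | *w*D = 40%, *w*P = 60% | *w*D = 20%, *w*P = 80% |
|---|---|---|---|
| 20% | 0 points | 12% − 8% = 4 points | 16% − 4% = 12 points |
| 40% | 0 points | 24% − 16% = 8 points | 32% − 8% = 24 points |
| 60% | 0 points | 36% − 24% = 12 points | 48% − 12% = 36 points |

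The true difference is zero throughout. Swapping the two dismissal rates reverses the sign. Bias therefore needs judgement to differ by arm, and its direction is not fixed. An investigator aware of active treatment might attribute more events to the drug, or might dismiss more of them.

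**2. What do the other data recover?**

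| Source | Gives | Does not give |
|---|---|---|
| Schedule of assessments (Table 4) | TSH, FT4, FT3 and resting pulse at day 0, day 14 and weeks 4, 6, 12 and 24 | Event severity, duration or causality; anything between visits, including the 12 weeks from week 12 to week 24 (24 − 12 = 12) |
| Vital signs at infusions (Intervention) | Pulse before, every 15 minutes during, and for 1 hour after the infusion | Attribution to the infusion or to the disease |
| Medical notes (Safety reporting) | The AE as documented by the clinician | A coded record that can be analysed by arm without a chart review |
| Serious AE reporting (Safety reporting) | All serious events | Non-serious events |

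Biochemical hypo- and hyperthyroidism at visits can thus be tabulated by arm whatever the investigator judges. Adverse reactions cannot be rebuilt from these sources without going back to the notes, because they need a causality assessment.

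**3. Tachycardia around an infusion.**

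Intervention sends infusion-related reactions to the AE record, and Table 3 counts tachycardia among grade 3 signs. Safety reporting names tachycardia among events that may go unreported if judged usual for the disease. In a thyrotoxic patient one episode can be read either way, and the article does not say which recording rule then governs. The classification also matters because Table 3 links the third occurrence of a grade 3 or greater reaction to permanent discontinuation.

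**The case against.** The strongest reply is that exempting disease events which are measured as outcomes is common practice. FT3, FT4 and TSH are secondary outcomes measured repeatedly, serious events are still reported, and progression worse than expected is still recorded. This largely holds for biochemical thyroid status. It does not hold for attribution, which is what an adverse-reaction outcome requires.

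A second reply is that the article condenses a longer protocol that is not shown, which may name assessors or database flags. It may also mean only that such events are not sent on to the sponsor. That limits how firmly the blinding point can be put: the investigator is not stated to be blinded, but is not stated to know the dose either. The exemption itself is a stated rule and not an omission.

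Three stronger readings are tempting, and the document does not support them.

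- *The safety comparison is biased.* Part 1 of the check shows zero distortion under equal dismissal, so the most that can be said is that it could be biased.
- *The dropped events are lost for good.* They should be in the medical notes, and thyroid function and pulse are collected on schedule.
- *Table 3 contradicts the exemption.* Intervention can fairly be read as governing whatever is classed as an infusion reaction, and the exemption covers only events judged usual for the disease. What remains is an overlap that has not been reconciled.

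Nor is it a measure of bias that one event moves an arm of 3 by 33 percentage points (1/3). That follows from the arm size and is true of any event.

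Finally, Trial status says that stage 2 is underway, so a change cannot affect the interim dose decision. It can still improve the final safety comparison.

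**Conclusion.** The point stands as a cheap improvement to recording. The protocol article lets an investigator who is not stated to be blinded keep non-serious hyperthyroidism, hypothyroidism, tachycardia and bradycardia out of the reported AEs. At least two of these are plausible treatment effects. This could bias the comparison of adverse reactions between arms, in either direction.

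The size is unknown. It ranges from nothing under equal dismissal to 4 to 12 points in the moderate scenario and 12 to 36 points in the extreme one, all on assumed inputs. The conclusion rests on reading the exemption as keeping these events out of the trial's AE data. The wording of the neighbouring rule on disease progression, which speaks of recording, supports that reading. Separately, the provisions on tachycardia around infusions overlap.

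**What to change.** 1. Enter these events in the trial database as AEs, with date, severity, investigator causality and a flag for consistency with Graves' disease. Limit any exemption to expedited reporting, and leave the existing duty to report serious AEs unchanged.
2. Tabulate AEs by arm twice, with and without flagged events, so that a reader can see how far the comparison depends on the judgement.
3. Reconcile Intervention, Table 3 and Safety reporting on how tachycardia during or shortly after an infusion is recorded. Which rule should govern is for the trial's clinicians and sponsor.

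Cost: additional AE data entry for 30 patients and, for those already enrolled, a look-back at the medical notes. No extra visits or tests are needed. Causality assigned retrospectively may be influenced by knowledge of the allocation, so entries from the look-back should be marked as such.

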### End of trial

The end of the trial is defined as last patient last visit. Treatment allocation will be revealed to all participants (and their general practitioner/referring clinician where applicable) by letter at the end of the trial, with contact details to discuss if required. At the end of their participation in the study, participants will return to standard NHS care.

### Payment

No payment will be made to participants for taking part in this trial, although reasonable travel expense reimbursement including taxis will be made for trial visits.

### Data management

The Clinical Data Management System (CDMS) used to capture trial data is Red Pill, supplied by Sealed Envelope. Users have individual password-protected user accounts appropriate to their trial duties (eg, randomisation, data entry, monitor). Patients are identified on the CDMS using a unique participant ID. Data monitoring will include a mixture of central, off-site and on-site approaches and will be outlined in a risk-based monitoring plan prior to the start of the trial. The trial-specific Data Management Plan will include details of how the validity and quality of data will be monitored and managed. As far as possible, validations will be built into the CDMS and additional manual validations will be detailed in the Data Validation Plan. Trial monitoring will be performed by the NCTU as per the monitoring plan and the trial is also liable to audit by the trial sponsor and regulator.

Until publication of the trial results, access to the full dataset will be restricted to the Trial Management Group (TMG) and to authors of the publication. Requests for anonymised data should be directed to the lead author.

### Analysis

The primary analysis will assess whether there is a significant dose–response using percentage reduction in serum TRAb concentration from baseline to 12 weeks using the intention-to-treat population (participants analysed according to randomisation allocation).

To do this, we will calculate a contrast-based test statistic at a one-sided 5% type I error rate.^21^ If this test statistic is significant, we will test whether there is a mean difference in the outcome between individual doses and placebo using a suitable linear model. We will also perform a simple test of all placebo participants versus all daratumumab patients using a linear model that adjusts for presence of eye disease. We will also fit quadratic and three-parameter Emax models to assess dose–response.^22^ This analysis will inform selection of the most suitable dose for subsequent trials. Exploratory analyses using subgroups of patients including by gender, smoking status, presence of TED and change in serum TRAb will be undertaken.

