### Inclusion criteria

Patients ≥18 years old.Recent-onset Graves’ disease (within 12 months) (defined as date of first thyroid function test showing hyperthyroidism (FT4 and TSH) in current episode).TRAb concentrations above 10 U/L (on Roche or Brahms TRAb-binding assays).One or more of:Pretreatment severe hyperthyroidism (FT4 ≥50 pmol/L or FT3 ≥15 pmol/L).Persisting hyperthyroidism despite more than 12 weeks of antithyroid drug therapy (defined as FT3 above the upper limit of the reference range following 12 weeks of carbimazole treatment at a dose of 40 mg or more daily (or equivalent dose of propylthiouracil)).Inflammatory thyroid eye disease (defined as Clinical Activity Score ≥3) or thyroid dermopathy.Large (visible) goitre (WHO grade III).Two or more relapses (three episodes in total) despite completing 12 months or more of medical treatment on each occasion. Relapse is defined as FT3 above the upper limit of the local reference range.For women of childbearing potential, willing to use a highly effective contraceptive method during their participation in the trial.Able to understand and speak sufficient English to complete trial procedures.Willing and able to provide informed consent prior to any trial procedures taking place.

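### The final primary test is written on percentage reduction with no stated baseline TRAb term, while the interim model and power simulation use a log scale; one log-scale, baseline-adjusted model would be modestly more efficient

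*Protocol article*

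**What the plan says.** The Analysis section of the protocol article assesses dose–response "using percentage reduction in serum TRAb concentration from baseline to 12 weeks using the intention-to-treat population". For this, "we will calculate a contrast-based test statistic at a one-sided 5% type I error rate". It does not say whether the final contrast is computed on the percentage or the log scale, and it names no baseline TRAb term.

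If the contrast is significant, the next step tests for a "mean difference in the outcome between individual doses and placebo using a suitable linear model", with covariates left open. One covariate is named in that section, for a supporting analysis: "a simple test of all placebo participants versus all daratumumab patients using a linear model that adjusts for presence of eye disease".

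Elsewhere the article uses logs. The interim Emax model is "fitted to the logarithm of the percentage change in TRAb from baseline to week 12". Under Statistical size calculations, the simulation takes a normally distributed log outcome with SD 0.5.

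Baseline TRAb is available for everyone. Eligibility requires "TRAb concentrations above 10 U/L (on Roche or Brahms TRAb-binding assays"), with no upper limit, and the row "TSH, FT4, FT3, TRAb" in Table 4 (Assessments) is marked at screening, day 0 and every later visit. Under Trial design, stage 1 has five groups of three without stratification.

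**The concern.** The final test is described on a different scale from the one on which the trial was powered and its interim decision was modelled. If log ratios have a constant SD, percentage change does not: its SD shrinks as the reduction grows. A contrast test that pools one variance across doses is then less efficient on the percentage scale than on the log scale.

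Percentage change can also stay correlated with baseline. With small unstratified arms and no upper limit on entry TRAb, a baseline term is the usual way to use that correlation. At stake is some precision in a trial of 30 patients, and a clear definition of the outcome in the primary model.

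**Working it through.** **1. The article's own figures.** Inputs from Statistical size calculations: log SD 0.5, 5% placebo reduction, 27 evaluable patients, one-sided 5%. The outcome was taken as −log(week 12/baseline), with no baseline covariate. The simulation had stage 1 of 5×3 patients, an Emax fit with the interim rules, 12 further patients over three arms, and a final contrast t-test (2,500 replicates).

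| Scenario | Table 5 | Recomputed |
|---|---|---|
| 1: plateau 80%, ED50 3 mg/kg | >99% | 99.8% |
| 2: plateau 60%, ED50 1 mg/kg | 92% | 93.4% |
| 3: plateau 60%, ED50 3 mg/kg | 83% | 84.0% |
| 4: null | 3.2% | 2.9% |

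Recruitment also reproduces: 27/0.9 = 30. The stated power therefore stands on the log-ratio scale without a baseline term.

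**2. Unequal variance on the percentage scale.** By the delta method, SD(percentage change) ≈ 0.5 × mean ratio.
- At ratio 0.50: 0.5 × 0.50 = 0.25, the article's 25%.
- Placebo, ratio 0.95: 0.475.
- Plateau, ratio 0.40: 0.20.

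The SD falls by a factor of 0.95/0.40 = 2.375 and the variance by 2.375² ≈ 5.6.

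**3. Cost of the covariate, fixed five-arm design, scenario 2.** With N=27 and 5 dose groups, estimating one slope inflates variance by about 1 + 1/(27−5−2) = 1.05. Let r be the correlation of log change with log baseline.

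- Contrast scores s = d/(d+1) = 0, 0.333, 0.5, 0.75, 0.9, so Σ(s−s̄)² = 0.500.
- Log effect = ln(0.95/0.40) = 0.865.
- With 27/5 = 5.4 per group, noncentrality = 0.865 × √(5.4×0.500)/0.5 ≈ 2.84.
- Unadjusted log change, 22 df: power 86.6%.
- Log ANCOVA, 21 df, variance factor 1.05(1−r²): 85.1% at r=0, 86.3% at 0.2, 87.9% at 0.3, 90.0% at 0.4, 92.7% at 0.5.
- Break-even on variance: 1.05(1−r²) = 1, so |r| = √(1−1/1.05) ≈ 0.22.

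If log baseline and log week 12 have equal variance s² and correlation rho, Var(change) = 2s²(1−rho) and Var(ANCOVA) = s²(1−rho²). The ratio is (1+rho)/2. Multiplied by 1.05, it is 0.79 at rho 0.5, 0.89 at 0.7, 1.00 at 0.9 and 1.02 at 0.95. Neither r nor rho is in the article, so both are shown as assumed ranges.

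**4. The three analyses compared by simulation.** Scenario 2, groups of 6, 5, 5, 5 and 6, 6,000 replicates, log baseline taken as normal without truncation at the entry limit.

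| r (absolute) | Percentage change | Log change | Log ANCOVA |
|---|---|---|---|
| 0 | 86.2% | 88.6% | 87.4% |
| 0.2 | 86.2% | 88.7% | 88.5% |
| 0.3 | 86.1% | 88.6% | 90.0% |
| 0.5 | 85.7% | 88.3% | 93.9% |

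Type I error was 4.8% to 5.8% for all three (4,000 replicates). Log change is 88.6% here against 86.6% in step 3 because the two extreme groups have one more patient. Both fixed-design figures are below the two-stage 93.4%, so only differences between analyses should be read from steps 3 and 4.

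**The case against.** The strongest reply is that this is a condensed article and the SAP is not shown. Covariates are routine SAP content, and the dose-versus-placebo model is left open. That stands: silence does not prove an unadjusted analysis. What remains is what the Analysis section does state, a percentage outcome, and its mismatch with the log scale used elsewhere.

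Four stronger readings are tempting, and the document does not support them.

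- **That the trial uses raw percentage change throughout.** The interim model and the power simulation are on a log scale. Only the final test's scale is left unfixed.
- **That adjustment is free, or cuts variance by 5 to 25%.** The (1+rho)/2 ratio gives that range for rho from 0.9 down to 0.5, but omits the 5% cost. Net, it is about 0 to 21%, measured against log change, and becomes a small loss at rho 0.95. Wide baseline spread does not help: with change SD 0.5, 0.25 = 2s²(1−rho), so rho 0.9 means s ≈ 1.12 and rho 0.5 means s = 0.5. Wider spread goes with higher rho and a smaller gain.
- **That chance imbalance goes uncorrected in arms of three.** A change score already removes much of the baseline level. The primary contrast uses all arms, and placebo reaches 3+5 = 8 with two stage 2 doses, or 10 to 11 with one.
- **That the trial is underpowered without the covariate.** Table 5 reproduces without it.

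The 2 to 3 point loss also depends on the log model. If percentage change had a constant SD of 25 points, the variance argument in step 2 would not apply. The article's simulation, however, assumes the log model.

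**Conclusion.** The point holds as an efficiency improvement. Under the article's log SD of 0.5, testing on the percentage scale costs about 2 to 3 points of power against a log analysis. Log ANCOVA did better than percentage change at every r examined, by about 1 point at r=0, 4 at 0.3 and 8 at 0.5. Against unadjusted log change, the covariate loses about 1 point at r=0, breaks even near |r| = 0.22 and gains 5 to 6 points at 0.5. Since the article gives no correlation, a gain from the covariate itself is plausible but cannot be asserted.

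No stated figure fails. These sizes rest on a lognormal ratio, a fixed five-arm approximation to the adaptive design, and scenario 2.

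One wording matter supports fixing the model explicitly. Taken literally, the log of a percentage reduction is undefined for anyone whose TRAb does not fall. With a 5% mean and 25% SD, that is Φ(−5/25) ≈ 42% of placebo patients. The power figures reproduce when the outcome is read as the log of the week 12 to baseline ratio.

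**What to change.** Before the final analysis, specify log(week 12 TRAb) as outcome with log(baseline TRAb) as covariate. Use it in the contrast test, the dose-versus-placebo models, the pooled test (keeping eye disease) and the final Emax fit. Report adjusted geometric mean ratios converted to percentage reductions, and keep percentage change as description. If the SAP already does this, no change is needed beyond stating it.

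The cost is one degree of freedom, about 5% variance inflation at N=27, and a rerun of the power simulation with the covariate over a range of correlations. No new data are needed. Trial status says stage 2 was underway and only participants are blinded, so the change should be dated, justified without reference to outcomes by arm, and documented as made after the interim analysis.
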